## Abstract

**Background:**

Military members are at elevated risk of operational stress injuries, including posttraumatic stress disorder (PTSD) and moral injury. Although psychotherapy can reduce symptoms, some military members may experience treatment-resistant PTSD. Multimodular motion-assisted memory desensitization and reconsolidation (3MDR) has been introduced as a virtual reality (VR) intervention for military members with PTSD related to military service. The 3MDR intervention incorporates exposure therapy, psychotherapy, eye movement desensitization and reconsolidation, VR, supportive counselling, and treadmill walking.

**Objective:**

The objective of this study is to investigate whether 3MDR reduces PTSD symptoms among military members with combat-related treatment-resistant PTSD (TR-PTSD); examine the technology acceptance and usability of the Computer Assisted Rehabilitation ENvironment (CAREN) and 3MDR interventions by Canadian Armed Forces service members (CAF-SMs), veterans, 3MDR clinicians, and operators; and evaluate the impact on clinicians and operators of delivering 3MDR.

**Methods:**

This is a mixed-methods waitlist controlled crossover design randomized controlled trial. Participants include both CAF-SMs and veterans (N=40) aged 18-60 years with combat-related TR-PTSD (unsuccessful experience of at least 2 evidence-based trauma treatments). Participants will also include clinicians and operators (N=12) who have been trained in 3MDR and subsequently utilized this intervention with patients. CAF-SMs and veterans will receive 6 weekly 90-minute 3MDR sessions. Quantitative and qualitative data will be collected at baseline and at 1, 3, and 6 months postintervention. Quantitative data collection will include multiomic biomarkers (ie, blood and salivary proteomic and genomic profiles of neuroendocrine, immune-inflammatory mediators, and microRNA), eye tracking, electroencephalography, and physiological data. Data from outcome measures will capture self-reported symptoms of PTSD, moral injury, resilience, and technology acceptance and usability. Qualitative data will be collected from audiovisual recordings of 3MDR sessions and semistructured interviews. Data analysis will include univariate and multivariate approaches, and thematic analysis of treatment sessions and interviews. Machine learning analysis will be included to develop models for the prediction of diagnosis, symptom severity, and treatment outcomes.

**Results:**

This study commenced in April 2019 and is planned to conclude in April 2021. Study results will guide the further evolution and utilization of 3MDR for military members with TR-PTSD and will have utility in treating other trauma-affected populations.

**Conclusions:**

The goal of this study is to utilize qualitative and quantitative primary and secondary outcomes to provide evidence for the effectiveness and feasibility of 3MDR for treating CAF-SMs and veterans with combat-related TR-PTSD. The results will inform a full-scale clinical trial and stimulate development and adaptation of the protocol to mobile VR apps in supervised clinical settings. This study will add to knowledge of the clinical effectiveness of 3MDR, and provide the first comprehensive analysis of biomarkers, technology acceptance and usability, moral injury, resilience, and the experience of clinicians and operators delivering 3MDR.

**Trial Registration:**

ISRCTN Registry 11264368; http://www.isrctn.com/ISRCTN11264368.

**International Registered Report Identifier (IRRID):**

DERR1-10.2196/20620

## Introduction

### Background

Posttraumatic stress disorder (PTSD), a mental health condition triggered by experiencing or witnessing a terrifying event, can be life-altering. Characterized by enduring symptoms related to negative cognitive intrusions, avoidance, hypervigilance, and alterations in mood, arousal, and reactivity [1], PTSD is the most common mental illness experienced by military members and veterans [2-4], and remains the predominant focus of most military and veteran health research and care [5-8]. PTSD prevalence is persistent and may increase over time [9], characterized by complexity and a wide variance internationally within military and veteran populations [10]. Among US military members deployed during the War on Terror, PTSD prevalence estimates reach up to 19% [10] compared to 5.3% for Canadians [11], 2.7% to 4% in UK military members [12], and 3% for military members from the Netherlands [13]. A recent meta-analysis reported that overall rates remained high (at approximately 23%) for US veterans following 9-11 [14] and the incidence of PTSD increased to 16% for Canadian veterans [15].

Isolated or cumulative traumatic experiences can also cause long-term psychological and spiritual struggles, including depression, anxiety, moral injury [5,16], and suicide [17]. Moral injury—a separate trauma syndrome that results from exposure to ethically or virtuously injurious experiences such as witnessing or participating in acts that transgress personal morals and values [18]—has been posited as a potential key comorbidity, and a compounding and complicating factor of PTSD [19,20].

The classification of treatment-resistant PTSD (TR-PTSD) has been adopted for the many veterans who do not experience a clinically significant reduction in symptoms following receipt of evidence-based treatment. International PTSD guidelines consistently demonstrate trauma-focused cognitive behavioral therapy, cognitive processing therapy, prolonged exposure, and eye-movement desensitization and reprocessing (EMDR) to be the gold-standard and first-line treatments for PTSD. However, it is equally acknowledged that military members and veterans consistently have poorer clinical outcomes than their civilian counterparts in these treatments [21-23]. Although general recommendations for optimizing psychotherapies (ie, using untried or complementary modalities) and utilizing secondary pharmacological interventions (ie, mood stabilizers, antiadrenergic agents/hypnotics, or atypical antipsychotic agents) have been suggested [24], specific evidence-based TR-PTSD therapies or protocols are lacking.

### Multimodular Motion-Assisted Memory Desensitization and Reconsolidation

Multimodular motion-assisted memory desensitization and reconsolidation (3MDR) is an emerging virtual reality (VR)-assisted therapy being studied with military members and veterans in the Netherlands, United States, United Kingdom, and Canada. It is hypothesized that the combination of trauma modalities in 3MDR may contribute to its potential effectiveness. The key elements of 3MDR therapy include: (1) engaging in exposure to traumatic material whereby avoidance patterns are minimized or broken; (2) experiencing emotions in the here and now that are evoked while the traumatic memories are being retrieved, and giving expression to these; and (3) reintegrating (reconsolidating) memories and sensory along with affective information associated with the trauma via a dual task (Figure 1) [25,26]. It is also thought that the combination of elements involved in 3MDR work collectively to facilitate the memory reconsolidation necessary to reduce the intensity of traumatic memories and subsequent PTSD symptoms. These include (1) exposure to VR visual imagery and auditory input, (2) walking, (3) a dual-attention task, and (4) therapeutic context and relationship [25,26]. A brief description of each element follows.

**Figure 1 figure1:**
[figure not shown]
Schematic overview of the augmentation strategies applied in the framework of the multimodular motion-assisted memory desensitization and reconsolidation (3MDR) intervention and its outcomes. Used with permission [25]. PTSD: posttraumatic stress disorder.

#### Exposure to Visual and Auditory Input

Emotional dysregulation and numbing are increasingly being considered as crucial components to address in PTSD treatment, especially for veterans who appear to more actively withhold emotional responses and use numbing as a coping mechanism [27]. Viewing affective pictures is thought to increase emotional engagement, and has been found to elicit physiological response patterns, which are higher for unpleasant pictures [28,29]. However, in addition to looking at affective pictures [30], auditory input such as music is noted to be a strong emotional trigger [31]. As self-selected music can elicit the retrieval of significantly more autobiographical memories in people with dementia [32,33], it is considered that optimal memory recollection may likewise be elicited by music for those with PTSD. Patients diagnosed with PTSD have indicated that music evokes (traumatic) memories, and enables them to access and discuss these memories [25,34,35]. Visual and auditory components are therefore central to 3MDR because of their believed ability to evoke potentially repressed or numbed emotions.

#### Walking

Among those with PTSD, walking toward an image of a traumatic memory has been found to increase engagement, decrease avoidance [36], potentially support the formation of new cognitive and emotional experiences related to the traumatic event, and contribute to reconsolidation of the traumatic memory [25]. Walking seems to facilitate consolidation of fear-related and traumatic memories. This occurs through bilateral movement [25], associated increases in brain-derived neurotrophic factor levels [37], approach behaviors toward feared cues and challenging working memory [33], increasing expression of associative memory [38], enhancing divergent thinking (which facilitates accessing emotional and cognitive networks associated with the traumatic memory) [37,39], allowing for new memories to surface [39], and reducing somatic and dissociative symptoms [40]. Walking throughout 3MDR’s platform phase is thought to be foundational to the therapy.

#### Dual-Attention Task

The dual-attention task component of 3MDR aims to facilitate processing and reconsolidation of traumatic memories and utilizes aspects of EMDR [31,41,42]. In traditional EMDR interventions, participants are asked to retrieve aversive memories and rate their vividness and emotional intensity [41-45]. They are then asked to recall the memories while making eye movements or performing a bilaterally stimulating task [41-45]. Within the 3MDR intervention, this task requires the participant to visually track a horizontally moving ball across the screen in the foreground of a traumatic image while calling out numbers displayed on this ball. Reconsolidation theory posits that a memory, while it is being recalled, becomes pliable for some time in which new information may be added [25,43]. Working memory is considered to be taxed when the brain is required to simultaneously perform two tasks. The first task (ie, viewing a traumatic picture) receives less attention and attenuates the vividness and emotional tone of the memory [44-46]. While participants are recalling traumatic memories in the course of 3MDR, more context or new information can be consolidated so that memories are not experienced as a current threat or as emotionally charged [25].

### Therapeutic Context and Relationship

The therapeutic setting of 3MDR is an active side-by-side rather than passive position, which impacts both the physical context and therapeutic alliance. The patient is supported throughout the process by a therapist who is standing alongside, and, more importantly, is also viewing the same traumatic material while the patient is recalling their traumatic event. This emotional participation in treatment is increased by the psychotherapeutic approach where the therapist asks the patient to describe the image, and their memory, somatic responses, cognitions, and emotions. Lower emotional valence and processing of the traumatic memories is expected, with new learning and the full traumatic network activated along with intervening in the reconsolidation process [25].

Findings from a 3MDR proof-of-concept study [40] and two initial randomized controlled trials (RCTs) [26,47] involving military members and veterans with combat-related TR-PTSD have been promising. In the published RCTs, decreases in PTSD symptom severity from baseline to the trial end point were significantly greater for the 3MDR group as compared to those of the control group with medium to large effect sizes [26,47]. Notably, these effects were maintained for weeks after the conclusion of the 3MDR intervention and a low dropout rate was noted in both studies. Although the results of the primary outcome, a reduction in PTSD symptoms, were favorable, variable results in the secondary outcomes were obtained, and many questions about 3MDR remain, warranting further examination.

### Overall Aims

This protocol describes a novel study to assist with the knowledge translation of the underpinnings of 3MDR as a therapeutic intervention. The primary study aim is to investigate whether the 3MDR intervention reduces symptoms of combat-related TR-PTSD and moral injury compared with treatment as usual among Canadian Armed Forces service members (CAF-SMs) and veterans. The study will be the first of its kind to examine the technology acceptance and usability of the Computer-Assisted Rehabilitation ENvironment (CAREN) VR system for 3MDR by participants, 3MDR clinicians and operators, as well as the impact of delivering 3MDR on clinicians and operators. Further, the longitudinal nature of the study will facilitate analysis of the longevity of possible 3MDR treatment effects for up to 6 months postintervention. This study will also address the possible effect of 3MDR on the constructs of moral injury and resilience. Further, as examination of relationships of psychological and biological factors to effective PTSD treatment has become critically important in attempts to understand the pathogenesis of TR-PTSD and to identify novel therapeutic targets [48-50], biomarker measurements and machine learning will be employed. Classifying neuropsychiatric disorders on the basis of objective and practical biomarkers aims to inform the diagnosis and selection of therapeutic approaches [51-54]. Machine-learning analysis will attempt to develop predictive models that can be used for individual diagnosis and prediction of the course of illness and effectiveness of treatment. Biomarker and machine learning utilization is a unique and novel addition to the study of 3MDR that has yet to be incorporated into other 3MDR studies internationally.

The main research questions to be addressed include: (1) Will participants’ combat-related TR-PTSD and moral injury symptoms, and associated behavior and physiology, change after an intervention of 3DMR therapy compared with treatment as usual? (2) Will peripheral multiomic biomarkers related to traumatic stress (ie, blood and salivary proteomic and genomic profiles of neuroendocrine, immune-inflammatory responses, and microRNA) be modified by the 3MDR intervention and show utility for predicting patient outcomes posttreatment? (3) What are the 3MDR clinicians’, operators’, and participants’ perceived technology acceptance and usability of 3MDR on the CAREN system? (4) What is the overall participant experience of the 3MDR intervention and comparability to PTSD therapies that the participants had previously engaged in? (5) Will 3MDR clinicians and operators experience perceived or secondary traumatic stress, or a change in their professional quality of life as a result of delivering 3MDR?

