### Specific Objectives

The first objective of the study is to examine the effect of 3MDR therapy on combat-related TR-PTSD and moral injury symptoms, behaviors, and physiological measures for CAF-SMs and veterans who have not benefited from other trauma therapies. The second objective is to examine the perceived technological acceptance and usability of 3MDR by CAF-SMs and veterans with combat-related TR-PTSD as well as 3MDR clinicians and operators. The third objective is to examine the effects of 3MDR on the operators and clinicians who provide this intervention to military members and veterans with combat-related TR-PTSD. In addition to conventional statistical analyses, the final objective of this study is to explore the application of machine learning in an attempt to identify individual data patterns that may predict diagnosis, severity, and potential treatment outcomes.

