### Hypotheses

Related to the objectives above, we have derived the following four hypotheses for this study.

Hypothesis 1: Participants’ symptoms of combat-related TR-PTSD will decrease during the 3DMR therapy compared with treatment as usual.

Hypothesis 2: CAF-SMs, veterans, 3MDR clinicians, and operators will perceive 3MDR to be a novel intervention with adequate perceived technology acceptance and usability.

Hypothesis 3: 3MDR operators and clinicians will not experience adverse mental health effects, including secondary trauma and stress, that affect their daily functioning as a result of 3MDR delivery.

Hypothesis 4: Machine-learning analysis will generate two accurate predictive models that may portend diagnosis, severity, and potential treatment outcomes in CAF-SMs and veterans with combat-related TR-PTSD.

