**Figure 2 figure2:**
[figure not shown]
Schematic overview of a single multimodular motion-assisted memory desensitization and reconsolidation (3MDR) session. A session consists of a preplatform phase (A), platform phase (B), and postplatform phase (C). Used with permission [25]. VR: virtual reality; SUD: Subjective Units of Distress scale.

In the context of the full-service hospital setting, a risk mitigation strategy will be implemented. Clinicians providing 3MDR who have vast experience with trauma-affected populations, including CAF-SMs and veterans, will be authorized to provide mental health services. Clinicians and operators will continually assess the safety of participants during sessions, and will stop the intervention and implement codes or safety protocols if required. Participants will be debriefed after therapy to determine if they are safe to leave the site and prepared to follow their self-care and safety plan. Alternate participant transportation will be utilized for participants if required.

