Recruitment of 3MDR clinicians and operators (N=12) will be conducted through word of mouth among the six international 3MDR research teams located in the Netherlands, the United States (California and Maryland), the United Kingdom (Wales), and Canada (Alberta and Ontario). Clinicians and operators who have received training for 3MDR and completed 6 weeks of interventions will be eligible for a pre/post evaluation. Voluntary written informed consent will be obtained from all participants.

The control group will undergo screening for eligibility and baseline assessment, followed by 9 weeks of treatment as usual while the intervention group receives the 3MDR intervention. They will then be provided an opportunity to cross over into the intervention group.

For the introductory session, intervention group participants will become accustomed to the CAREN system by practicing the process associated with 3MDR, including walking on the treadmill while looking at a neutral image as the clinician guides them through the 3MDR protocol. The participant will be asked to provide (1) images reminiscent of the traumatic deployment event that preceded a PTSD diagnosis, ranked according to the emotional distress that each elicits (ie, from least to greatest level of distress); and (2) digital music tracks of a song that reminds them of their deployment and other sounds or music that provide positive feelings. A secondary purpose of this introductory session is also to transfer trust from their service provider to the 3MDR researchers and clinicians. One week after the introductory session, the 3MDR therapy will be initiated and participants will undergo 6 90-minute sessions.

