#### Objective 3: 3MDR Operators and Clinicians

The impact of delivering 3MDR will be examined with clinicians and operators using questionnaires related to technological acceptance, perceived stress, and professional quality of life prior to 3MDR training and on completion of a full course of 3MDR with a study participant (Table 2).

**Table 2 table2:** Time points of data collection for multimodular motion-assisted memory desensitization and reconsolidation (3MDR) clinicians and operators.

Construct to be measured	Measure	Week 1 (Baseline)	Week 9 (Post)
Technology Acceptance and Usability	UTAUT^a^ Questionnaire	X	X
Perceived Stress	PSS^b^	X	X
	SUDS^c^	X	X
	Subjective Interview		X
Professional Quality of Life	PQoL^d^	X	X
Secondary Stress	STSS^e^	X	X

^a^UTAUT: Unified Theory of Acceptance and Usability of Technology.

^b^PSS: Perceived Stress Scale.

^c^SUDS: Subjective Units of Distress Scale.

^d^PQoL: Professional Quality of Life Scale.

^e^STSS: Secondary Traumatic Stress Scale.

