#### Objective 3: 3MDR Operators and Clinicians

Owing to the small anticipated sample size, nonparametric statistical analysis with the Wilcoxon signed-rank test will be employed to assess the outcome measures addressing clinician and operator stress. Qualitative interviews will be thematically analyzed as described above.

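### The staff objective is worded as an effect of delivering 3MDR, but its quantitative evidence is an uncontrolled before-and-after change in 12 people

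*Protocol article*

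**What the plan says.** The causal wording appears in several places of the protocol article:

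- Overall Aims, research question 5, asks about perceived or secondary traumatic stress "or a change in their professional quality of life as a result of delivering 3MDR".
- Specific Objectives: "The third objective is to examine the effects of 3MDR on the operators and clinicians who provide this intervention".
- Hypothesis 3 predicts no adverse mental health effects "that affect their daily functioning as a result of 3MDR delivery".
- Study Timeline and Data Collection, Objective 3: "The impact of delivering 3MDR will be examined with clinicians and operators using questionnaires".
- Discussion, Projected Outcomes, again treats secondary stress as a consequence of delivering the therapy.

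The design behind these statements is also printed. Under Recruitment: "Recruitment of 3MDR clinicians and operators (N=12) will be conducted through word of mouth", drawing on six international teams, and "Clinicians and operators who have received training for 3MDR and completed 6 weeks of interventions will be eligible for a pre/post evaluation". Under Objective 3 and in Table 2 there are two questionnaire assessments, one before training (week 1) and one after a full course (week 9), with an interview at the second. Under Data Analysis, Objective 3: "nonparametric statistical analysis with the Wilcoxon signed-rank test will be employed to assess the outcome measures addressing clinician and operator stress". The interviews are analysed thematically, and Triangulation of Data plans to set quantitative and qualitative findings against each other.

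**The concern.** A signed-rank test on paired scores asks whether scores moved over the interval. It cannot say why. Every member of the staff sample delivers 3MDR. The waitlist and treatment-as-usual arm consists of patients, so it gives no comparison for staff. Perceived stress, secondary traumatic stress and professional quality of life can all change over about nine weeks for reasons unrelated to 3MDR.

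The error can run both ways. A rise with another cause could be read as harm from 3MDR. A rise that 3MDR did cause could be masked if stress eased elsewhere. The second matters because Hypothesis 3 predicts the absence of harm, which makes this in effect a question of staff safety.

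The article sets a different standard for its patient question: research question 1 and Hypothesis 1 are both framed against treatment as usual. The staff question makes an equally causal claim with nothing to compare against, and the Limitations section does not mention it.

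**Working it through.** **No figure to reproduce.** The article gives N=12 for staff with no sample size or power calculation for this objective. The Sample Size section concerns the patient trial and is not an input here.

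**What the design estimates.** Write a staff member's paired change as D = δ + d + e, where δ is the effect of delivering 3MDR, d is the background change over the same interval, and e is individual variation.

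- One group, before and after: the mean of D is δ + d. Only the sum is identified.
- With a comparator whose mean change is d, the difference in mean change is (δ + d) − d = δ.

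More assessments of the same group, or more people in it, would estimate δ + d more precisely but would not separate the two terms.

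**Illustration of the consequence.** Inputs:

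- n = 12, from Recruitment.
- Two-sided .05, stated under Data Analysis for Objective 1 and assumed to apply here.
- Normal paired differences with SD 1: an assumption.
- δ = 0, and d the same for all staff, in SD of the paired difference: assumptions. The documents give no value for d, so a range is shown.

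The exact signed-rank test with n = 12 rejects when the smaller rank sum is 13 or less. Its true size is 2 × 87/4096 = 0.0425. Simulated rejection rates (40,000 replicates per row):

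| Background drift d (SD) | 3MDR effect δ | P<.05 |
|---|---|---|
| 0 | 0 | 4.3% |
| 0.3 | 0 | 13.8% |
| 0.5 | 0 | 31.7% |
| 0.8 | 0 | 66.7% |

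Because only δ + d enters, the same table serves other cases. A real 3MDR effect of 0.5 SD with no drift is also detected 31.7% of the time. A real effect of 0.5 SD offset by easing of 0.5 SD elsewhere gives 0.5 − 0.5 = 0, so rejection returns to about 4%.

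**Contrast.** With a hypothetical comparator of 12 staff sharing the drift, and an exact Mann-Whitney test on change scores (4,000 replicates per value of d), rejection with δ = 0 was 4.3%, 4.8% and 4.6% at d = 0, 0.5 and 0.8. It stays near nominal whatever the drift.

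**The case against.** The strongest reply is one of proportion and purpose. This is the third objective, in 12 people, openly described as a pre/post evaluation with a small expected sample, in a mixed-methods study. An uncontrolled design is acceptable for exploratory staff data, and the post-delivery interviews plus triangulation are a planned source on what staff themselves attribute any stress to. That stands. The interviews should be part of the interpretation. They record perceived cause, however, and do not supply the missing d.

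Some stronger readings are tempting but not supported by the documents:

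- *That a significant result will be reported as harm from 3MDR.* No decision rule says so. The test is only said to assess the measures, and Hypothesis 3 is limited to effects on daily functioning, which a score shift alone would not establish.
- *That 14%, 32% or 67% is the plan's false-positive rate.* These figures require one drift common to all staff. Influences that differ from person to person around zero mainly add noise, for which the no-drift figure of about 4% is closer.
- *That nine staff already have paired scores.* Results counts 5 clinicians and 4 operators who finished the pre/post measures or the interview, so the number of pairs is not stated.
- *That other trauma work is not recorded, or that staff carry a concurrent trauma caseload.* The first is inferred from the silence of a condensed article. For the second, the Intervention section's "Clinicians providing 3MDR who have vast experience with trauma-affected populations, including CAF-SMs and veterans" describes experience, not current workload.

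**Conclusion.** The point holds as a mismatch between claim and design. Five places in the article attribute staff stress or professional quality of life to delivering 3MDR, while the quantitative data are a single-group comparison before and after in 12 people. Background change and a 3MDR effect are confounded in both directions, and Limitations does not say so. This is not detail left out by condensation: the question, hypothesis, group, time points and test are all printed, and they do not fit together.

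The conclusion rests only on the absence of a described staff comparator. Its practical size cannot be derived from the documents; the percentages above are hypothetical and depend on an assumed common drift. The point does not depend on low power, or on reconciling the Recruitment wording (eligible after training and six weeks of interventions) with a baseline taken before training. It does not touch the randomized comparison or the primary aim. It should be corrected because it changes what Objective 3 is entitled to conclude.

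**What to change.** 1. Reword research question 5, Objective 3, Hypothesis 3, and the matching text under Study Timeline (Objective 3) and Projected Outcomes as change between the pre-training and post-delivery assessments, without attributing it to 3MDR.
2. Report the paired change on each scale with a confidence interval, not the test result alone.
3. Limit the conclusion to change over the delivery period, interpreted alongside the interviews as staff members' perceived causes.
4. Add the missing staff comparator to Limitations.
5. Optionally, record non-3MDR trauma workload for staff not yet assessed, as descriptive context only. It cannot be collected at baseline from staff who have already finished, and it would not identify a causal effect in 12 people.

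Steps 1 to 4 need no new participants or data. The price is a weaker, non-causal conclusion for a secondary objective. If a causal answer is wanted, a staff comparator is needed, at the cost of recruiting and assessing further staff.
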